### Data collection

#### Data collection method and assessment of outcomes

At baseline, we will collect demographic, clinical, cost, and health-related quality of life data and photograph lesions. Counselling and pregnancy test will be done for all females of reproductive age at screening (see Table 1). Data on pain assessment using the Visual Analogue Scale (VAS) will be collected fortnightly following randomisation at each scheduled visit.

#### Participant timelines

Each participant will have 15 scheduled review visits at Week 2, 4, 6, 8 and then monthly until one year following initiation of antimicrobial treatment (Table 1). Individuals will be followed for a minimum of 20 weeks. Visits beyond 20 weeks will be conducted within the framework of routine care.

#### Wound photography and size measurement

Wound diameter and area will be recorded by digital photography and measured by computer planimetry using a Silhouette Wound Imaging System (ARANZ, Wellington, New Zealand) at each clinical visit. The Silhouette camera captures an image of the wound. A tracing of the wound boundary will be generated and the wound dimensions will be automatically calculated. These measurements will enable calculation of healing rate at Week 4 and predicted healing time in relation to lesion size and type. The mean diameter, area, depth and volume of the wound will be measured. The same measurements will be made for non-ulcerated lesions (nodule, plaque and oedema).

#### MU viability assessment

Samples will be taken before and during treatment to assess persistence of viable MU. Swabs will be taken from the undermined edges of ulcerated lesions or FNA samples from the centre of non-ulcerative (nodule, plaque and oedema) lesions at Weeks 2, 4, 6, 8, 12 and 16 (if lesions are not healed) for the combined MU 16S rRNA reverse transcriptase/IS2404 real-time qPCR^10,11^.

#### Secondary infection and bacterial culture

Wounds will be assessed clinically for secondary infection at each time point. In the context of new purulent discharge, a single swab shall be taken for microbiological assessment. Swabs will be plated onto agar and cultured for the identification of potential secondarily infecting bacteria. Organisms will be identified and antibiotic sensitivity testing performed using standard microbiological protocols.

#### Resource use and cost data

At every scheduled visit, data will be collected on costs incurred by the household that can be attributed to a householder having BU and/or seeking treatment for BU. At Week 0, all costs incurred since onset of BU symptoms will be collected. At each follow-up visit, costs related to BU since the last visit will be collected. These include costs of medicines, hospitalisation, consultation, transportation as well as opportunity costs relating to having and treating BU (for example, missed work or school). Socioeconomic data on household income, expenditure (frequent and non-frequent items) and asset ownership will also be collected at Weeks 0, 2, and 4 to establish a month of income and expenditure data based on prospective data collection with a maximum of 2 weeks’ recall. Information on how households cope with the burden of BU will also be collected at each follow-up visit.

The programme-level costs of resources used in implementing the new interventions (high-dose rifampicin and DACC dressings) are expected to include costs of training health workers, intervention planning, and implementation. These costs will be collected from the project’s activity and financial records; the value of donated items will be estimated based on market prices. Where necessary, government sources will also be consulted for relevant cost data.

#### Health-related quality of life

Health-related quality of life data will be collected at every scheduled visit (Table 1) using the EQ-5D-5L instrument developed and validated for Ghana by the EuroQol research foundation. The tool is a brief self-reported preference-based measure which focuses on five dimensions (mobility, self-care, usual activities, pain/discomfort and anxiety/depression) each with five levels of functioning (*e.g.* no pain-1, slight pain-2, moderate pain-3, severe pain and extreme pain). In addition, we will collect data on patient’s emotional state, experience of pain or itch, and any physical deformity to inform assignment of weights for disability-adjusted life-years (DALYs).

#### Monitoring

An external Good Clinical Practice (GCP) monitor will be appointed to monitor all aspects of the study, with respect to current GCP, to ensure compliance with government regulations. Prior to the start of the study, the investigator will be informed of the frequency of monitoring visits and will be given reasonable notification before each visit by other designated monitoring bodies.

### Data management

Each participant will be allocated a unique participant identification number which will be used on all electronic documents and photographs. Data will be collected by researchers onto the REDCap platform hosted on a secure server at the School of Medical Sciences (SMS) of the Kwame Nkrumah University of Science and Technology (KNUST). Lesion photographs taken using the ARANZ device will be saved to the secure Silhouette Central SQL server. Data will be encrypted and access will be password-restricted.

#### Study documentation and data safety

All data collected will be confidential and stored according to GCP standards. Study members with direct access to the data will take all necessary precautions to maintain confidentiality. The study databases will be password-protected and access to password will be authorised by the Principal Investigators. Electronic data files will be stored on operated and dedicated servers at KNUST.

Privacy of the study participants will be maintained by assigning study participants a unique participant identification number. All data, samples and laboratory results will be recorded and analysed with only this unique identification number and no personal identifiers will be used. Analyses of data will be performed on copies of the original data files always ensuring raw data accessibility.

### Statistical analysis

#### Statistical methods

Statistical analysis of outcomes will be carried out blind to treatment allocation. The primary and secondary efficacy outcome analysis will be carried out using a modified intention-to-treat (ITT) population of individuals who were PCR-positive for BU at baseline. An analysis on a per-protocol population will also be carried out. Analysis will follow a pre-specified statistical analysis plan.

#### Populations to be analysed

Analyses will be carried out using two different types of dataset: modified ITT and per-protocol.

##### The modified ITT dataset

The modified ITT population will consist of all patients who were PCR positive for BU at baseline.

##### The per-protocol dataset

A per-protocol analysis will be carried out in addition to the primary ITT analysis. The per-protocol dataset will include all individuals who (i) completed the intended course of antimicrobial treatment; (ii) received appropriate wound care; (iii) did not report any major protocol violations; and (iv) did not take any prohibited medications during the study.

#### Primary outcome

For the primary outcome of mean time to clearance of viable MU, we will use regression models with a Gaussian link function to estimate the mean difference between the two arms. This will be reported with a 95% confidence interval.

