### Outcomes

#### Primary outcome

The primary outcome measure is the mean time to clearance of viable MU.

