#### Sample size

The sample size is based on existing data which demonstrated a mean time to clearance of viable MU with standard dose rifampicin and Vaseline gauze dressings (standard care) of eight weeks^10^, with a standard deviation of four weeks. Assuming a lower standard deviation of three weeks for high-dose rifampicin (intervention), 100 participants (randomised 1:1) would enable us to detect a reduction of two weeks in mean time to RNA clearance with 80% power and 5% significance. In addition, 100 participants would also allow us to see an increase of approximately 27% in the proportion of patients with healed wounds at 20 weeks in the high-dose rifampicin arm. This is based on a conservative assumption that 50% of wounds would be healed at 20 weeks with DACC dressings and the standard dose rifampicin^10^. Assuming a loss to follow-up rate of 10%, we therefore plan to recruit 112 participants to ensure that at least 100 participants are followed up for a minimum of 20 weeks.

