#### Secondary outcomes

For secondary outcomes, appropriate models will be used to examine the effect of the intervention; for example, modified Poisson regression models will be used to estimate risk ratios for binary outcomes. Measures of effects will be reported with 95% confidence intervals. If there is evidence of non-normality in the continuous outcomes, then non-parametric bootstrapping will be used to estimate bias-corrected 95% confidence intervals.

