## Figures and Tables

**Table 1 T1:** Schedule of procedures for study participants. BU: Buruli ulcer.

Activity	Screening	Week 0	Week 2	Week 4	Week 6	Week 8	Monthly	12 Months	Treatment failure
Written informed consent	X								
Inclusion and exclusion criteria and socio-demographics	X	X							
Randomisation		X							
History and physical exams		X	X	X	X	X	X	X	X
Clinical assessment	X	X	X	X	X	X	X	X	X
Adverse events			X	X	X	X	X	X	X
Clinical assessment of the patient and lesion		X	X	X	X	X	X	X	X
Measurement of lesion size		X	X	X	X	X	X	X	X
Photograph of lesion by digital camera	X	X	X	X	X	X	X	X	X
Counselling and testing for pregnancy	X			X		X			
Swab/FNA for PCR	X	X							X
Swab/FNA for 16S rRNA (0, 2, 4, 6, 8 weeks and then monthly if not healed)		X	X	X	X	X	X		X
VAS		X	X	X	X	X	X	X	X
Functional limitations assessment		X	X	X	X	X	X	X	X
Health-related quality of life (QALY, DALY) for economic evaluation		X	X	X	X	X	X	X	X
Household costs of BU and of care seeking		X	X	X	X	X	X	X	
Socioeconomic status		X	X	X					

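### Time to clearance is interval- and right-censored, but the primary analysis is a Gaussian mean-difference regression that needs one exact time per participant, so the estimate can be biased in either direction

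*Protocol article*

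**What the plan says.** Outcomes, Primary outcome: "The primary outcome measure is the mean time to clearance of viable MU". Statistical analysis, Primary outcome: "we will use regression models with a Gaussian link function to estimate the mean difference between the two arms", with a 95% confidence interval.

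The swab schedule is given twice. MU viability assessment places the samples "at Weeks 2, 4, 6, 8, 12 and 16 (if lesions are not healed", so the last one is at Week 16. The row in Table 1 reads "Swab/FNA for 16S rRNA (0, 2, 4, 6, 8 weeks and then monthly if not healed". It is marked under Monthly and blank under 12 Months. Participant timelines adds: "Individuals will be followed for a minimum of 20 weeks".

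Two other passages bear on the point. Statistical analysis, Secondary outcomes has a fallback: "If there is evidence of non-normality in the continuous outcomes, then non-parametric bootstrapping will be used" to obtain confidence intervals. Missing data expects little to be missing and would consider inverse probability weighting or multiple imputation if losses exceed expectation or differ by arm. Neither mentions censoring.

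**The concern.** Clearance happens between visits and is seen at the next swab. The gap is 2 weeks up to Week 8 and about 4 weeks after that, so using the visit week as the clearance time rounds later times up by more. A participant still positive at the last swab, or lost before a negative one, has no clearance time at all. A lesion that heals before a negative swab leaves the time undefined as well, because swabbing then stops.

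A linear model for a mean difference needs a number for each of these people, and the article gives no rule for supplying it. The two schedule statements also disagree on when observation ends, which decides who is right-censored. At stake is the trial's single primary estimate and the power claimed for it.

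**Working it through.** **Inputs (Sample size section).** Control mean: "standard dose rifampicin and Vaseline gauze dressings (standard care) of eight weeks", "with a standard deviation of four weeks". Intervention SD 3 weeks; reduction 2 weeks, so 8 against 6; 80% power; 5% significance; 100 evaluable, 112 recruited for 10% loss.

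**The plan's own figure reproduces.** With every time fully observed and a two-sided test, n per arm = (1.960 + 0.842)² × (4² + 3²) / 2² = 7.85 × 25 / 4 = 49.1, rounded up to 50, so 100 in total. Power at 50 per arm: 2 / √(25/50) − 1.960 = 0.868, giving 80.7%. Recruitment: 100 / 0.9 = 111.1, so 112. The calculation makes no allowance for censoring or for rounding to visits.

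**Effect of the schedule, no losses.** True times were simulated with means 8 and 6 and SDs 4 and 3, and clearance was recorded at the first scheduled swab after it occurred. The shape is an assumption, so three were tried. Power is for 50 per arm, equal-variance comparison. The monthly column continues swabs to Week 52; stopping one visit earlier, as the blank 12 Months cell implies, still gives about 2.2.

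| Shape | Uncleared at Week 16, control / intervention | Dropped: difference, power | Set to Week 16: difference, power | Monthly swabs: difference |
|---|---|---|---|---|
| Normal | 2.3% / 0.0% | 2.00, 74% | 2.15, 79% | 2.24 |
| Gamma | 4.3% / 0.6% | 1.80, 68% | 2.04, 77% | 2.24 |
| Lognormal | 4.4% / 1.0% | 1.80, 73% | 2.02, 80% | 2.24 |

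Two errors oppose each other. Dropping removes slow clearers and narrows the difference. Rounding up to the visit widens it, because more control times fall in the 4-week gaps. With normal times and dropping, the two cancel.

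**Adding loss.** Take 56 per arm, 10% loss spread evenly over 0 to 20 weeks (assumed), and swabs to Week 16. Under gamma times 8.6% of control and 4.2% of intervention participants have no value.

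- Dropping them gives about 1.8 weeks with power of about 70% to 71% (gamma) and up to 77% (lognormal).
- Setting non-clearers to Week 16 gives about 2.0 weeks with power of about 79% to 80% (gamma), 81% (normal) and 83% to 84% (lognormal). Repeat runs differ by about a point.

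**Dependence on the scoring rule.** Add participants who never clear to the gamma scenario.

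- 5% in control and 10% in intervention: dropping gives 1.79 weeks, Week 16 scoring gives 1.49.
- 10% in control and 5% in intervention: dropping gives 1.80, Week 16 scoring gives 2.27.

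Dropping hardly responds to which arm fails to clear.

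**A restricted mean to Week 16.** Under gamma times the restricted means are 7.88 and 5.99, so the difference is 7.88 − 5.99 = 1.89 weeks.

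**The two schedules.** Participant timelines counts 15 visits: Weeks 2, 4, 6 and 8, then monthly to one year. With 4-week months that is 4 + (52 − 8)/4 = 4 + 11 = 15. Weeks 12 and 16 therefore fit both statements, and only the end of swabbing conflicts.

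**The case against.** The strongest reply is that no passage tells the analyst to drop non-clearers. The article refers to a pre-specified analysis plan that is not shown, and scoring a non-clearer is a detail commonly left to such a plan. A one-line scoring rule recovers most of the power within the same Gaussian comparison. Few participants are involved: under gamma times without loss, about 0.043 × 50 ≈ 2 control participants and fewer than one intervention participant remain positive at Week 16. The sample size already allows for 10% loss, and the Missing data section offers weighting or imputation.

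Much of this stands. It limits the size of the problem and rules out a fixed direction. A reader might infer that the estimate is biased toward no effect and that the stated power is lost. The documents do not support that: it assumes dropping, a skewed shape, and more non-clearers in the control arm. Nor is Table 1 open-ended, since its viability row is blank at 12 Months.

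Three things remain. The article itself fixes the model, and an analysis plan using a time-to-event method would depart from it. Weighting or imputation is conditional and aimed at missing data; a participant still positive at the last swab may have attended every visit. The bootstrap, even if read as covering the primary outcome, changes the interval and supplies no unobserved times.

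**Conclusion.** The stated model does not fit the data the schedule will produce, and the primary estimate depends on a scoring rule and an end of swabbing that the article does not settle. The estimate can be biased either way. Under the protocol's means and SDs, the no-loss figures with swabs to Week 16 run from 1.80 to 2.15 weeks, and monthly swabbing gives about 2.24, against a true 2.0. That is roughly −0.2 to +0.24 weeks. Power runs from about 68% to 84% according to scoring rule, shape and loss, against 80% planned.

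These figures rest on assumed distribution shapes, loss timing and never-clear fractions. Healing before a negative swab was not simulated, so its effect is unquantified. The phrase *Gaussian link* is only a wording slip for a Gaussian family with identity link. This is a should-fix point: the correction is clear and cheap, but the likely bias is modest under the full schedule.

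**What to change.** 1. Make the primary analysis an interval-censored time-to-event model on the interval from last positive to first negative swab, right-censored at the last swab. A grouped-time proportional-hazards model or a parametric accelerated-failure model would serve.
2. Use the modified ITT set as the article defines it, with no added condition. Someone without a post-baseline swab is simply censored at time zero.
3. Report the difference in restricted mean time to clearance to a stated horizon, with a bootstrap 95% CI. Week 16 is one example, being a visit that both schedule statements include.
4. State one rule for lesions that heal without a negative swab: either healing closes the interval at that visit, or the participant is censored at the last positive swab. Run the other as a sensitivity analysis.
5. Reconcile MU viability assessment (last swab Week 16) with Table 1 (monthly if not healed, blank at 12 Months).
6. Correct the *Gaussian link* wording wherever that term is kept.

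The cost is protocol and analysis-plan wording plus modest programming, settled before unblinding. The estimand becomes a restricted mean, with an expected difference of about 1.89 weeks to Week 16 under gamma times rather than the 2.0 in the sample size section, and this should be stated. In one gamma simulation with 56 per arm and 10% loss, a grouped-time test had about 81% power and 5.0% type I error. Most of its gain over 70% comes from keeping participants rather than dropping them.

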#### Secondary outcomes

For secondary outcomes, appropriate models will be used to examine the effect of the intervention; for example, modified Poisson regression models will be used to estimate risk ratios for binary outcomes. Measures of effects will be reported with 95% confidence intervals. If there is evidence of non-normality in the continuous outcomes, then non-parametric bootstrapping will be used to estimate bias-corrected 95% confidence intervals.

### Economic evaluation

The incremental costs, cost-effectiveness, and equity of using HR and DACC-coated wound dressings relative to alternative strategies will be assessed from provider, household, and societal (*i.e.*, combined provider and household) perspectives, consistent with reference case specifications^29^, including the reference case for Ghana if finalized by the end of the study. We will assess actual practice in the trial and develop a model to explore how costs and effects may be expected to vary outside the trial setting in a “real-world” context. The model will combine trial data with additional data sources to inform decisions regarding a potential switch in policy to a treatment strategy incorporating high-dose rifampicin and DACC-coated dressings. The within-trial analysis will be based on the ITT dataset and will compare the costs and outcomes associated with HR+DACC and SR+DACC interventions. In the model we develop, we will project findings over a longer time horizon, if appropriate, and will also include a third comparator, SR plus standard gauze dressings, which reflects current practice recommended by WHO. Health outcomes associated with this current practice strategy will be modelled based on secondary literature and health-related quality of life estimates associated with specific clinical outcomes estimated within our trial; costs will be modelled based on resource use information in the literature^7,9^ and unit costs estimated within our trial.

Results of the cost-effectiveness analysis will include mean costs and effects (with distributions for each) under each strategy compared. If one strategy is both more costly and more effective than another, the incremental cost-effectiveness ratio will be presented and compared against relevant cost-effectiveness thresholds^30,31^. Deterministic and probabilistic sensitivity analyses will be conducted to explore the sensitivity or robustness of findings to uncertainty and heterogeneity in key parameter values. Results will be presented on the cost-effectiveness plane and using cost-effectiveness acceptability curves. Where more than two alternative strategies are compared, the cost-effectiveness frontier and expansion pathway will be identified^32^.

Both financial costs, which reflect actual monies paid, and economic costs, which reflect the full value of resources used will be assessed. All costs pertaining to research activities (*i.e.*, data collection which does not affect outcomes) will be excluded. We will include both the recurrent costs associated with each participant treated, and also the “start-up costs” incurred by providers in switching from current practice to HR and DACC dressings.

The “effectiveness” in the cost-effectiveness analysis will be assessed using quality-adjusted life-years (QALYs) and disability-adjusted life-years (DALYs). Both combine measures of length and quality of life into a single metric, which allows the results of economic evaluations to be compared across different health areas. For QALYs, utility scores between 0 (dead) and 1 (Perfect health)^33^ will be generated for each participant at each time point by combining population value sets with health states collected with the EQ-5D-5L. If a population value set for Ghana is available by the time of analysis, it will be used; otherwise, we will explore if and how findings may vary when value sets for other African countries (*e.g.* Uganda^34^, Ethiopia^35^) are used. For DALYs, disability weights between 1 (death) and 0 (Perfect health) will be assigned to each participant at each time point by using their responses to patient experience questions (designed for this purpose) to map them onto one of the six skin-related disability states (3 levels, with or without pain or itch)^36^. For each health state, the standard disability weight (mean and distribution) will be applied. Area under the curve methods^37^ will be applied to generate total QALYs gained and total DALYs lost for each participant.

Equity dimensions will be examined by assessing variations in incremental costs and benefits of the interventions across socioeconomic and/or demographic groups.

### Missing data

Every effort will be made to obtain required data at each scheduled evaluation from all participants who have been randomised. Any missing data will be identified and attempts made to obtain until received, confirmed as not available, or the trial is at analysis. Only a small volume of missing data is anticipated and it is therefore unlikely that this will need to be accounted for in any analysis.

However, if necessary we will consider using inverse probability weighting or multiple imputation if missing data were larger than expected and/or there was differential attrition between the trial arms. We would also attempt to ensure that the reason for the differential attrition was fully understood.

